## **1.2 Objectives**

### **Aims**

1. To reduce the time until a patient walks with one assist through the addition of an anabolic steroid (nandrolone) and resistance exercise to deconditioned ICU patients.
2. To determine whether nandrolone reduces hospital length of stay for deconditioned ICU patients.
3. To determine whether nandrolone reduces the time to return to work for deconditioned ICU patients (of working age).
4. To document changes in grip strength and limb muscle strength in the two groups in the follow-up period after enrolment.

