### **HYPOTHESES:**

Nandrolone will improve muscle strength and physical functioning at hospital discharge and at follow-up 3 months after enrolment.

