### **Outcomes**

#### **Primary and secondary outcomes**

Primary outcome:

1. Time to walking with one person assisting (days from admission to ICU).
2. Hospital length of stay

Secondary outcomes:

1. Change in muscle strength as measured by the medical research council muscle strength (MRC) sum score - enrolment to discharge (note some ICU patients may not be able to participate in full MRC scoring, score will be extrapolated from available limbs) (9)
2. Grip strength (measured by hand held dynamometry)

3. Functional activity at hospital discharge (measured by physiotherapy staff using the Chelsea critical care physical assessment tool (CPAx (7)) and follow-up phone call at 3 months post discharge (using SF-36).
4. Hospital length of stay
5. Time to return to work (days) (for those working pre ICU).

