### **1.1 Statistical analysis and Sample size**

Trial will be prospectively registered on ANZCTR.

Efficacy of intervention will be analysed on an intention to treat basis. The analysis population is the intention to treat population defined as all study participants except for those who do not consent to use of data. There will be no imputation for missing data. A per protocol analysis will also be conducted including all participants with adherence to study medication of >80% of total study duration.

Normally and non-normally distributed data will be presented as mean and standard deviation (SD), and median and interquartile range (IQR), respectively. Between-group comparison of parametric data will be provided as mean difference and confidence interval and analysed using Student's t test. Between-group comparison of non-parametric data will be presented at median difference and analysed using the Mann-Whitney U test. For dichotomous data, frequencies and percentages will be presented and between-group analysis will use Fischer's Exact or Chi-squared test as appropriate. The numbers at risk in each group and the number and proportion of events observed will be reported, as well as the equivalent absolute risk difference, relative risk ratio and corresponding 95% confidence intervals. Survival time from randomisation until day 60, according to treatment group will be displayed as Kaplan-Meier curves and analysed using a log-rank test. Estimates of hazard ratios for survival, with corresponding 95% CI and P values, will be obtained from the Cox proportional hazards models incorporating treatment group alone, and independent covariates used in the multivariate models. Secondary analysis will also be conducted adjusting the primary outcome variable for prespecified baseline covariates (age, gender, APACHE-II score, BMI) in a transformed multivariable linear regression model including

baseline univariate variables with a  $p < 0.05$ . For all outcome analyses a two-sided P value of  $< 0.05$  will be considered significant.

Baseline variables recorded to demonstrate that the groups are comparable; if this is not demonstrated, *post-hoc* adjustments to correct for differences will be applied.

Sample size calculation: 60.

This is based on several different assumptions and outcome measures:

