### **Blinding**

Study medication will be provided blinded to treatment providers and trial participants through the use of a placebo. Syringes will be masked (sticker/alfoil) to prevent the contents being visualised to the administering nurse. Outcome assessment at 3 months, including SF-36, return to work will be conducted by a blinded research team member via telephone.

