## **DATA COLLECTION, MANAGEMENT, AND ANALYSIS**

### **Data collection methods**

#### **Data Collection**

Data will be collected on a prespecified eCRF (RedCap - Research Electronic Data Capture - a secure web application for building and managing online surveys and databases) supported by a study-specific data dictionary and including checks of logical consistency and automatic query generation.

The following data will be collected:

- Age
- Gender
- ANZICS APD number

- Admission type (elective vs. emergency)
- ICU admission source (i.e. Emergency Department vs. ward vs. theatre vs. other hospital)
- Chronic APACHE co-morbidities
- APACHE-III admission diagnosis
- Illness severity based on the on the APACHE-II and III scores and risk of death, and “ANZ Risk of Death” models score
- ICU or HDA mortality
- ICU or HDA LOS
- Total duration of mechanical ventilation
- Total duration of vasoactive medication requirement
- Incidence and duration of renal replacement therapy
- Hospital mortality
- Post-ICU ward LOS
- Hospital disposition (home vs other acute care facility vs rehabilitation)
- ICU readmission
- Hospital readmission
- Day 60 mortality
- Inflammatory markers (CRP, Procalcitonin and WBC count at enrolment, ICU discharge and hospital discharge)
- BMI, weight at hospital admission, pre-admission medications.
- Baseline SF-36, FIM score and Barthel Index, to determine the patient’s pre-existing functional status (based on status two weeks prior to admission to ICU, from patient or surrogate).
- **Measurement of variables:**
  - **1. Laboratory tests**
    - Pregnancy test in women of child bearing age
    - Baseline: sex hormone binding globulin, testosterone.

- Routine blood tests will occur as planned by treating clinicians, and will collect:
- Haemoglobin, white cell count, albumin, urea and creatinine, alanine transferase.
- Lipids at baseline and at day 15-21.
- **2. Strength and weight measurements**
- a) Weekly: Hand grip strength, weight (kg) and MRC.
- **3. Other measures**
- Physiotherapy received - Duration of rehabilitation physiotherapy and mobility achieved (ventilation physiotherapy treatments will not be counted).
- Nutrition received - Caloric intake (kcal/total), Protein intake (g/total), Food intake (% of meals).
- **Follow-up**
- Phone call follow-up at 3 & 6 months using the SF-36 score , and asking about return to work (see script page).

*Pre-specified Subgroups:*

BMI at enrolment < 20

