Admission cause :sepsis, neurological, post surgical.

Data will be collected by trained research co-ordinators at each site. Patients and/or their next of kin will be asked to provide three possible points of contact (home and close family contact details) to the research staff prior to discharge. Day 90& 180 (post hospital discharge) SF-36 will be conducted over the phone by a trained assessor.

For data collected by research co-ordinators at each site, data quality and protocol standardisation will be optimised by arranging a start-up meeting, providing an early on-site monitoring visit, regular feedback to each centre via phone and the trial web-site, and a monthly newsletter. A complete study procedures manual will be produced. All study personnel will have 24 hour access to the study coordinating centre to resolve any questions.

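### Time to return to work has no rule for patients who have not returned or have died, and no named horizon; the stated tests then compare returners only, which can hide or reverse a real effect

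*Protocol*

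**What the plan says.** All references are to the protocol.

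- **Aims.** The third aim reads "To determine whether nandrolone reduces the time to return to work for deconditioned ICU patients (of working age".
- **Primary and secondary outcomes.** Secondary outcome 5 is "Time to return to work (days) (for those working pre ICU". It has no day zero, no end of window, and no rule for a patient who is not back at work or has died. The first primary outcome, in the same list, does have an origin (ICU admission).
- **Statistical analysis and Sample size (1.1).** Continuous data get Student's t test or the Mann-Whitney U test. On gaps in the data: "There will be no imputation for missing data". Kaplan-Meier curves, the log-rank test and Cox models are named only for survival, and the survival window runs from randomisation to day 60.
- **Blinding.** "Outcome assessment at 3 months, including SF-36, return to work will be conducted by a blinded research team member via telephone".
- **Data Collection.** "Phone call follow-up at 3 & 6 months using the SF-36 score , and asking about return to work". The same part of the protocol adds "Day 90& 180 (post hospital discharge) SF-36 will be conducted over the phone by a trained assessor", which names only the SF-36.
- **Anchor of the calls.** The outcome list has a "follow-up phone call at 3 months post discharge (using SF-36", whereas the hypothesis refers to "physical functioning at hospital discharge and at follow-up 3 months after enrolment".

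**The concern.** An outcome measured in days exists only for patients who reach the event. After critical illness many patients who worked before will not be back at work at 3 or even 6 months, and some will have died. A t test or Mann-Whitney test needs a value from everyone, and the protocol gives these patients neither a value nor a censoring time. The survival methods that could include them are tied to death and stop at day 60, before a call made 90 days after discharge.

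If non-returners drop out of the comparison, two things go wrong. The groups compared are selected by an outcome that treatment may affect, so randomisation no longer protects the comparison. And the main benefit one would hope for, that more patients get back to work, is removed from the estimate. If treatment brings slower patients back, they enter the treated arm as late returners and make that arm look worse.

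The unnamed horizon adds to this. Whether analysis stops at 3 or 6 months decides who has a value, and the protocol does not say whether the 6-month assessor is blinded.

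**Working it through.** **No figure to reproduce.** The protocol gives no return-to-work rate, event count or power for this outcome. The return rates below are assumptions. From the protocol come the total of 60 patients, 1:1 allocation (so at most 30 per arm, if every patient was working before ICU), two-sided 5% significance, and the 3- and 6-month calls, taken as days 90 and 180.

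**Model.** Exponential times to return, deaths ignored. With proportion p returned by day 180, the rate is λ = −ln(1 − p)/180.

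- Control, p = 0.30: λ = 0.001982, 1/λ = 504.66 days.
- Treated, p = 0.50: λ = 0.003851, 1/λ = 259.69 days.
- Rate ratio = ln(0.5)/ln(0.7) = 1.94.

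**Share without a value.** At day 180: 70% of control and 50% of treated patients. Returned by day 90: 1 − √0.70 = 16% and 1 − √0.50 = 29%, so 84% and 71% have no value at a 3-month stop.

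**Mean days among returners by day τ** = 1/λ − τ·e^(−λτ)/(1 − e^(−λτ)). At τ = 180:

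- Control: 504.66 − 180 × 0.70/0.30 = 84.7.
- Treated: 259.69 − 180 × 0.50/0.50 = 79.7.
- Gap: 5.0 days.

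**Mean days off work up to day τ, all patients** = (1 − e^(−λτ))/λ. At τ = 180:

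- Control: 504.66 × 0.30 = 151.4.
- Treated: 259.69 × 0.50 = 129.8.
- Gap: 21.6 days.

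The returners-only comparison keeps 5.0/21.6 = 23% of the effect.

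**Other assumptions**

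| Assumption | Stop (day) | Gap among returners | Gap, all patients | Share kept |
|---|---|---|---|---|
| 30% vs 50% at 6 months | 90 | 1.3 | 6.4 | 20% |
| 30% vs 50% at 6 months | 180 | 5.0 | 21.6 | 23% |
| 40% vs 60% at 6 months | 180 | 5.9 | 23.1 | 26% |
| 20% control at day 90, rate ratio 2 | 90 | 1.6 | 8.1 | 20% |
| 20% control at day 90, rate ratio 2 | 180 | 6.5 | 26.1 | 25% |
| 40% control at day 90, rate ratio 2 | 90 | 3.7 | 14.1 | 26% |
| 40% control at day 90, rate ratio 2 | 180 | 13.6 | 36.1 | 38% |

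**Reversal of sign.** Suppose 20% of controls return, spread evenly over days 30 to 90: mean (30 + 90)/2 = 60. Suppose the treated arm has the same 20% plus a further 20% spread over days 60 to 90: mean of the extra group (60 + 90)/2 = 75. The treated returner mean is (60 + 75)/2 = 67.5 days. Twice as many return, yet the treated arm looks 7.5 days slower.

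**Power at this trial's size.** Simulated Mann-Whitney tests, 30% vs 50%, 6-month stop. With 30 per arm, power is about 5% among returners only and about 33% with non-returners ranked last (separate runs gave 4–6% and 32–36%). With 15 per arm, if only half were working before ICU, it is at most about 5% against about 18%. Under a rate ratio of 2 with 30 per arm, returners-only power is 5–15% and a log-rank test with censoring at the last call has 28–66%, depending on the assumed control rate and the stop.

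**The case against.** **Dropping non-returners is not written anywhere.** A patient who says at the call that they are not back at work has a known status, so the rule against imputing missing data need not apply. Censoring or ranking last is not imputation. The intention-to-treat population covers everyone who does not refuse use of their data. This stands: a reader might infer that the protocol instructs a returners-only comparison, and it does not. It is the natural result of the tests named, because nothing stated gives a non-returner a value.

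**This could be left to the SAP.** The censoring date and the handling of death often are, and an SAP not shown may supply them. But the protocol goes beyond silence: it assigns continuous outcomes to tests that need a number from everyone and ties its time-to-event methods to survival over 60 days.

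**The 3- and 6-month statements can both be true.** The Blinding section says who makes the 3-month assessment; it does not say that this is the last call. A reader might infer that the sections conflict on when follow-up ends, and the text does not support that. What remains is that no horizon is named for the analysis and blinding at 6 months is unstated.

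**The loss may be overstated.** One might infer that a real benefit would vanish. In the scenarios it shrinks by 62–80% and reverses only in the constructed late-returner case. Correctly analysed, the trial would still often miss it. Nor does the pilot's 27% walking with one assist at discharge say anything direct about employment, so no return rate is drawn from it.

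**Conclusion.** The point holds in this form: the outcome behind Aim 3 has no rule for patients who do not return or who die, the analysis methods stated for it have no place for them, and no horizon is named. A returners-only comparison keeps roughly 20–38% of the true difference in the scenarios with a constant return rate, and can take the wrong sign if treatment adds late returners. These sizes rest on assumed return rates and, apart from the reversal example, on exponential times; deaths are ignored throughout. The protocol supplies none of these inputs.

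The repair removes a bias but does not make the trial well powered for return to work: about one chance in three under the main assumption, even if all 60 patients were working before ICU. For a secondary outcome tied to a named aim, the change should be made but does not threaten the trial's main result.

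**What to change.** - **Outcome list, Blinding and Data Collection:** name one horizon for return to work, the 6-month call that is already planned, and state that the blinded assessor makes it too. Count days from randomisation, and state whether the calls run from enrolment or from discharge.
- **Statistical analysis section:** analyse all patients working before ICU by a time-to-event method, with those not back at work censored at last contact and death treated as a competing event. As a sensitivity analysis, use a Mann-Whitney test with non-returners and deaths ranked last. Report the proportion back at work at 3 and 6 months by arm.
- **Aim 3:** match its population (working age) to that of the outcome (working before ICU).

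The cost is wording only, with no extra patients or calls. The small downside is that the result becomes a hazard ratio or a rank comparison rather than a mean or median number of days.

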### **1.1 Statistical analysis and Sample size**

Trial will be prospectively registered on ANZCTR.

Efficacy of intervention will be analysed on an intention to treat basis. The analysis population is the intention to treat population defined as all study participants except for those who do not consent to use of data. There will be no imputation for missing data. A per protocol analysis will also be conducted including all participants with adherence to study medication of >80% of total study duration.

Normally and non-normally distributed data will be presented as mean and standard deviation (SD), and median and interquartile range (IQR), respectively. Between-group comparison of parametric data will be provided as mean difference and confidence interval and analysed using Student's t test. Between-group comparison of non-parametric data will be presented at median difference and analysed using the Mann-Whitney U test. For dichotomous data, frequencies and percentages will be presented and between-group analysis will use Fischer's Exact or Chi-squared test as appropriate. The numbers at risk in each group and the number and proportion of events observed will be reported, as well as the equivalent absolute risk difference, relative risk ratio and corresponding 95% confidence intervals. Survival time from randomisation until day 60, according to treatment group will be displayed as Kaplan-Meier curves and analysed using a log-rank test. Estimates of hazard ratios for survival, with corresponding 95% CI and P values, will be obtained from the Cox proportional hazards models incorporating treatment group alone, and independent covariates used in the multivariate models. Secondary analysis will also be conducted adjusting the primary outcome variable for prespecified baseline covariates (age, gender, APACHE-II score, BMI) in a transformed multivariable linear regression model including

baseline univariate variables with a  $p < 0.05$ . For all outcome analyses a two-sided P value of  $< 0.05$  will be considered significant.

Baseline variables recorded to demonstrate that the groups are comparable; if this is not demonstrated, *post-hoc* adjustments to correct for differences will be applied.

Sample size calculation: 60.

This is based on several different assumptions and outcome measures:

1. Hospital length of stay, as sample of  $n=24$  per group has 80% power to detect a median difference of 3 days LOS (26 vs 23 days) with IQR 5.4 between independent groups (this is a conservative estimate as in the pilot, LOS results were 26 vs 36 days).
2. Time to walking with one-assist (ICU mobility scale). A sample of 24 per group has 80% power to detect a difference in proportions of 40 between the intervention and control groups, of patients walking with one assist at discharge (from a baseline of 27% in pilot).

To allow for loss to follow-up, the sample size number increased to 60.

Subgroup analysis: due to potential heterogeneity in patients, stratification based on MRC score,  $\geq 48$  (48 is an accepted cut off for ICU acquired weakness).

Economic evaluation:

An economic evaluation will be performed. Cost offsets from any reduction in LoS will be estimated separately for ICU stay and total hospital stay, and costed using hospital-specific per day costs. We will estimate QALYs using the SF-36 data converted to SF-6D using Australian population weights.(6)

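### Time to walking is defined as a duration but sized as a proportion, and the stated analysis gives no value to patients who never walk or who die first

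*Protocol*

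**What the plan says.** Under Primary and secondary outcomes, primary outcome 1 is "Time to walking with one person assisting (days from admission to ICU"). It is a number of days. No horizon is given, and no value for a patient who does not reach the event.

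The section Statistical analysis and Sample size then sets these rules:

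- **Population:** "The analysis population is the intention to treat population defined as all study participants except for those who do not consent to use of data".
- **Missing data:** "There will be no imputation for missing data".
- **Continuous data:** "Between-group comparison of parametric data will be provided as mean difference and confidence interval and analysed using Student's t test", or, if not normally distributed, "Between-group comparison of non-parametric data will be presented at median difference and analysed using the Mann-Whitney U test".
- **Time-to-event methods:** "Survival time from randomisation until day 60, according to treatment group will be displayed as Kaplan-Meier curves and analysed using a log-rank test". The Cox model is likewise described for survival.
- **Adjusted analysis of the primary outcome variable:** "in a transformed multivariable linear regression model including" baseline variables.
- **Dichotomous data:** Fisher's exact or chi-squared test.

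Sample-size item 2 is labelled as time to walking, but it powers a 40-point difference in the proportion "of patients walking with one assist at discharge (from a baseline of 27% in pilot"), with 24 per group and 80% power. The total of 48 is raised to 60 for loss to follow-up.

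**The concern.** Three parts of the protocol treat the same outcome in different ways. The definition is a duration, the adjusted model needs an observed number for each patient, and the sample size counts patients who have or have not walked by discharge. A proportion keeps non-walkers in the denominator. A t test, Mann-Whitney or linear regression on days has nowhere to put them unless a rule gives them a value, and the protocol gives none. The log-rank and Cox text does not fill the gap, because it concerns a different event (death) from a different origin (randomisation, not ICU admission).

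If only walkers are compared, the two groups are defined by something that happens after randomisation and that treatment is expected to change. The comparison is then no longer randomised, deaths before walking drop out, and a gain in the number of patients who walk does not count in itself. On the planning figures this affects about half the trial.

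Time to return to work, a secondary outcome, has the same gap for patients who never return.

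**Working it through.** **1. The plan's own figure.** Inputs from sample-size item 2: p1 = 0.27, p2 = 0.27 + 0.40 = 0.67, 80% power; two-sided 5% from the analysis text. The mean proportion is 0.47. With pooled variance and no continuity correction:

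n = [1.96 × √(2 × 0.47 × 0.53) + 0.842 × √(0.27 × 0.73 + 0.67 × 0.33)]² / 0.40² = 23.2, rounded up to 24 per group.

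The stated 24 is reproduced, with power of 81%. Also 48 / 0.8 = 60. So the calculation is sound, but for a comparison of proportions in which every patient counts.

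**2. How many patients would have a walking time.** This takes discharge to mean hospital discharge and leaves out deaths, whose rate is not given.

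| Per group | Control walkers (27%) | Nandrolone walkers (67%) | No time, both arms |
|---|---|---|---|
| 24 | 6.5 | 16.1 | 48 − 22.6 = 25.4 |
| 30 | 8.1 | 20.1 | 60 − 28.2 = 31.8 |

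The share without a time is 73% of controls, 33% of nandrolone patients, and 53% overall.

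**3. What that does to power.** The protocol gives no distribution of walking times, so three were assumed, each with 27% and 67% walking by discharge and no deaths. In the first two, discharge is set at day 26, borrowed from the length-of-stay planning figure. The two-sided Mann-Whitney test at 5% was simulated (4,000 to 5,000 trials) in walkers only, and in all patients with non-walkers ranked worse than any walking time.

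| Assumed walking times, 30 per group | Walkers only | All patients, worst rank |
|---|---|---|
| Log-normal, sigma 0.5 | about 24-25% | about 93-94% |
| Exponential | about 7-8% | about 88-89% |
| Same times among walkers in both arms (log-normal, median 18 days) | about 5% | about 85% |

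With 24 per group, walkers-only power is 19%, 7% and 5% in the same order, against about 88%, 81% and 74% for worst rank.

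**4. Comparison with the proportion itself.** On 27% against 67%, Fisher's exact test has exact power of 84% with 30 per group and 75% with 24. The uncorrected chi-squared test has 90% and 84%.

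**The case against.** A reader might infer that the protocol excludes non-walkers. It does not say so. A patient who was followed and did not walk is an observed non-event, not plainly a missing value, and the intention-to-treat definition keeps all who consent to data use. Nor is a t test or Mann-Whitney named for this outcome; tests are assigned by data type. Since sample-size item 2 treats the outcome as a proportion, the dichotomous rule (Fisher or chi-squared) is a documented reading that keeps everyone. All of this stands. It shows that the text supports two incompatible analyses. It does not remove the problem, because the outcome definition is in days and the adjusted analysis is a linear regression.

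A rule for non-walkers and deaths is often left to a statistical analysis plan, and one may exist. But such a plan would have to depart from the linear model, the restriction of time-to-event methods to survival, and possibly the ban on imputation. The inconsistency is therefore in the protocol itself.

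Sample-size item 2 does not say which discharge it means, while secondary outcome 3 specifies hospital discharge. If ICU discharge is meant, far more patients would have a time. For example, assuming ICU discharge at day 12, hospital discharge at day 26 and the log-normal model, about 82% and 98% would walk before leaving hospital. The counts above are conditional on this point.

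A reader might also infer that a real benefit would look like harm because the additional walkers are late ones. The documents give no walking times to support that. In the log-normal model nandrolone walkers are earlier (median about 17 against 20 days). The walkers' medians fall in the wrong order in about 11% of trials, almost never significantly. Power is lost mainly because few walkers remain and their times are cut off at discharge.

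**Conclusion.** The point holds as a mismatch between endpoint definition, stated analysis and sample size, with no value defined for patients who never walk or who die first. It should be corrected before unblinding, since the choice of reading can decide the result.

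The mismatch and the missing value can be read directly from the text. That only walkers would be compared is what follows from applying the rules to a duration; it is not a stated exclusion. The size (about 28 of 60 patients with a time, 8 against 20) rests on the planning proportions and on discharge meaning hospital discharge. The power contrast, roughly 5-25% against 85-94% with 30 per group, also rests on assumed time distributions and no deaths. The size of the loss varies with the distribution, but it was large under each one tried.

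**What to change.** State one primary analysis for outcome 1 that retains all randomised patients in the intention-to-treat population, up to hospital discharge. Choose one of the following in advance; they answer different questions and are not interchangeable.

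1. **Worst rank.** Mann-Whitney on walking time, with patients not walking by hospital discharge, and those who die before walking, ranked worse than any walking time. Say whether death ties with non-walking or ranks below it; that is a value judgement.
2. **Time to event.** Cumulative incidence of walking with one assist, with non-walkers retained to the stated horizon and death as a competing event.
3. **Proportion.** Redefine the outcome as walking with one assist at hospital discharge, as the sample size assumes. Name the test, because at 24 per group Fisher's exact gives 75% power rather than 80%.

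Replace the linear regression with an adjusted model that matches the choice, such as proportional-odds, competing-risks or logistic regression. State which discharge the 27% refers to. Give the power for the chosen analysis. Apply the same principle to time to return to work, so that those who never return are kept.

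The cost is wording in the protocol and analysis plan plus a restated power calculation. Mobility achieved and hospital mortality are already collected. A horizon beyond hospital discharge, such as day 60, would cost more, because no mobility assessment after discharge is described.

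### SF-36 and grip strength are compared by unadjusted tests although SF-36 has a collected baseline and grip an implied one; prespecified baseline adjustment would gain precision, by an amount the protocol does not let one fix

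*Protocol*

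**What the plan says.** **Tests.** Under Statistical analysis and Sample size, the protocol states: "Between-group comparison of parametric data will be provided as mean difference and confidence interval and analysed using Student's t test". Non-parametric data are to be "analysed using the Mann-Whitney U test". Neither test takes a covariate.

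**Planned adjustment.** The same section describes a secondary analysis "adjusting the primary outcome variable for prespecified baseline covariates (age, gender, APACHE-II score, BMI". It covers the primary outcome only, and no listed covariate is the baseline value of an outcome.

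**Conditional adjustment.** The section adds: "Baseline variables recorded to demonstrate that the groups are comparable; if this is not demonstrated", post-hoc corrections follow. It gives no threshold for comparability, no covariate list and no model.

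**Baselines.** Data Collection lists "Baseline SF-36, FIM score and Barthel Index, to determine the patient’s pre-existing functional status". This is recalled function from two weeks before ICU entry, reported by the patient or a surrogate. The same list has "Weekly: Hand grip strength, weight (kg) and MRC". Aim 4 (section 1.2) is to document how grip and limb strength change after enrolment. No separate enrolment grip measurement is scheduled.

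**Outcomes.** SF-36 is the functional measure at the follow-up call and the source of the QALYs. Grip appears among the secondary outcomes as "Grip strength (measured by hand held dynamometry", with no time point and no reference to baseline; the MRC score, by contrast, is defined as a change from enrolment.

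**The concern.** The hypothesis is that nandrolone improves strength and physical functioning at discharge and at three months. SF-36 and grip bear directly on it, in a trial of 60 patients with 24 per arm in the power calculation. Randomisation is stratified by site alone and both sexes are enrolled, so the design does not balance prior function or starting grip.

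Where a patient's baseline predicts the outcome, an unadjusted test treats that predictable variation as noise. The intervals are then wider than they need be, and chance differences at baseline pass into the point estimate. The remedy on offer is decided after the data are seen. If it is not triggered, it recovers no precision at all.

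**Working it through.** **Inputs from the protocol:** two-sided 5% level, 1:1 allocation, 24 per arm before the allowance for loss, 60 in total, no imputation of missing data. **Assumed:** rho from 0.2 to 0.7, and 80% unadjusted power. The protocol gives no rho, SD, effect size or power for SF-36 or grip.

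**The plan's own figure.** Walking with one assist, 27% against 27 + 40 = 67%, mean proportion 0.47:

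n = [1.96 × √(2 × 0.47 × 0.53) + 0.842 × √(0.27 × 0.73 + 0.67 × 0.33)]² / 0.40² = (1.383 + 0.544)² / 0.16 ≈ 23.2, so 24 per arm. Then 48 / 0.80 = 60, an implied 20% loss. The figure of 24 is reproduced.

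**Gain from adjustment.** ANCOVA multiplies the residual variance by 1 − rho². A t test with 24 per arm has 80% power at d = 0.826 SD. Adjusted power comes from the noncentral t with 2n − 3 = 45 df and noncentrality [d / √(1 − rho²)] × √(n/2). At rho 0.5 this is (0.826 / 0.866) × 3.464 = 3.30, giving 89.9%.

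| rho | 1 − rho² | 24 / (1 − rho²) | Power, formula | Power, simulated |
|---|---|---|---|---|
| 0.2 | 0.96 | 25.0 | 81.5% | 80.8% |
| 0.3 | 0.91 | 26.4 | 83.5% | 82.8% |
| 0.5 | 0.75 | 32.0 | 89.9% | 89.2% |
| 0.7 | 0.51 | 47.1 | 97.5% | 97.2% |

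The third column is the number per arm that an unadjusted test would need for the same precision. The simulation (100,000 trials per rho, normal data, 24 per arm) falls up to 0.7 points below the formula, which ignores the small cost of estimating the slope.

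Starting power matters too. At rho 0.5, 50% becomes 61.9% and 30% becomes 38.1% (normal approximation).

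**Chance imbalance.** The arm difference at baseline has SD √(2/24) = 0.289 SD, so P(|difference| > 0.3 SD) is about 30%. At rho 0.5 such a difference moves the unadjusted estimate by 0.5 × 0.3 = 0.15 SD. If comparability were judged by p < 0.05 (an assumption), the post-hoc rule would need a difference of 2.01 × 0.289 = 0.58 SD to act, so most imbalances above 0.3 SD would pass.

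**If grip were analysed as a change score.** Its variance factor is 2(1 − rho). At rho 0.7 this is 0.60 and power is 95.1%, against 97.5% for ANCOVA. At rho 0.5 it is 1.00, no better than the unadjusted test. At rho 0.3 it is 1.40 and power falls to 66%.

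**If patients without a baseline are dropped.** With 22 instead of 24 per arm, ANCOVA has 80% power at rho 0.3 and 78% at rho 0.2, so the gain is gone.

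**The case against.** The strongest reply is that nothing here is wrong. In a randomised trial an unadjusted comparison is unbiased, its error rate holds, and its confidence interval already allows for chance imbalance. These are secondary outcomes, and their covariates are often left to an SAP. All of that stands, and it limits the point to efficiency. It does not remove it, because the protocol names the tests and states which outcome is adjusted.

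A reader might infer that adjustment is wholly reserved for the primary outcome and that baseline differences are simply left in the results. The text does not support this: the post-hoc rule could reach SF-36, whose baseline is recorded. The rule is nevertheless a weak safeguard, since its trigger and model are open.

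A reader might also infer that the grip baseline is collected and then ignored. An enrolment reading is only implied, and Aim 4 speaks of changes, so a change score may be intended. That would use the first value, though never more efficiently than ANCOVA apart from the one degree of freedom for the slope.

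Finally, the baseline SF-36 is recalled pre-illness status, partly from surrogates, and may predict poorly after critical illness. With no imputation, a complete-case ANCOVA could lose patients. Both points stand. The first lowers the expected gain; the second must be dealt with in the fix.

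**Conclusion.** The point holds as a matter of efficiency and prespecification. The stated analysis of SF-36 and grip is valid but less precise than one that uses each patient's own baseline, and the only fallback is data-driven.

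It is tempting to say that about 10 points of power are lost. The documents do not support a single figure: it needs both rho near 0.5 and 80% unadjusted power, and the protocol claims 80% only for length of stay and walking. On the 80% assumption the formula gives a gain of about 2 to 18 points for rho 0.2 to 0.7, with SF-36 perhaps near the bottom of that range.

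Nor can it be said that imbalance distorts the economic result. The protocol describes neither a between-arm QALY test nor how baseline utility would be handled.

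**What to change.** In the statistical section:

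- Make linear regression (ANCOVA) the main analysis of SF-36 at follow-up and of grip strength, with terms for treatment arm, the patient's own baseline value of the same measure, and site (the stratification factor). Report the adjusted mean difference with its 95% CI.
- State that the first weekly grip reading is the enrolment value, and name the time point at which grip is compared.
- Keep patients with a missing baseline in the model, for example by mean imputation of the baseline covariate only, and word the no-imputation sentence to allow this.
- Replace the imbalance-triggered post-hoc rule for these outcomes.
- Keep the unadjusted test as a supporting analysis.
- If QALYs are compared between arms, include the baseline SF-6D value as a covariate.

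The cost is wording, a few degrees of freedom for baseline and site, and a defined grip reading at enrolment. No extra patients are needed. If rho is low, the gain will be small.
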